**Table pone.0332773.t002:** 

Demographics	Full name, medical record number, ED visit number, date of birth, postal code, sex, date and time of ED admission
**Source of information**	If not the patient, the source’s full name, date of birth, sex, and relationship to the patient will be recorded
**Sensory deficits**	Presence and type of visual and/or hearing impairments
**History of falls**	Number of falls in the past year, circumstances surrounding the falls
**Comorbidity**	Assessed using the Charlson Comorbidity Index (CCI) [12–15]
**Risk of falls**	Assessed using the Memorial Emergency Department Fall Risk Assessment Tool (MEDFRAT) and the Carpenter instrument [16,17]
**Frailty**	Assessed using the Clinical Frailty Scale (CFS) version 2.0 [18,19]
**Clinical severity**	Assessed using the National Early Warning Score (NEWS) 2 [20,21]
**Mood**	Assessed using the 15-item Geriatric Depression Scale (GDS-15) [22]
**Geriatric vulnerability**	Assessed using the PRO-AGE Score [10]
**Acute mental status change (delirium)**	Assessed using the Delirium Triage Screen (DTS) and Brief Confusion Assessment Method (bCAM) [23]
**Quality of life**	Assessed using the Euro Quality of Life Instrument – 5D (EQ-5D) [24]
**Functionality**	Assessed using the Katz Index, Barthel Index, and Lawton Scale [25–27]
**Cognitive performance**	Assessed using the 10-Point Cognitive Screener (10-CS) [28]

#### Medical and multidisciplinary staff interview.

A trained research assistant will interview medical and multidisciplinary staff concurrently with patient recruitment. The interview will follow the standardization of the original comfort cart validation study [3], using a Likert scale to answer the following questions.

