#### Sample size calculation.

The sample size calculation was based on the study by Lichen et al. (2021), which reported a difference of 0.98 on a Likert scale (ranging from 1 to 6) when assessing patient experience before and after the comfort cart intervention [3]. Considering a power of 90% and a significance level of 5%, 132 patients will be required in each group (pre- and post-intervention), totaling 264 participants.

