**Table pone.0332773.t003:** 

Questions adapted from Lichen et al. (2021)	
* Question *	* Response options *
*During the patient’s stay in the ED, what was his/her average level of comfort?*	Very comfortable; Comfortable; Somewhat comfortable; Somewhat uncomfortable; Uncomfortable; Very uncomfortable
*I feel that age-friendly care specific to the geriatric patient’s needs was provided*	Strongly agree; Somewhat agree; Neither agree nor disagree; Somewhat disagree; Strongly disagree
*I currently have access to non-pharmacological resources to provide comfort for geriatric patients*	Strongly agree; Somewhat agree; Neither agree nor disagree; Somewhat disagree; Strongly disagree
*Offering non-pharmacological resources to my patient increases my work burden by too much*	Strongly agree; Somewhat agree; Neither agree nor disagree; Somewhat disagree; Strongly disagree
Additional questions in the post-implementation phase	
*The Geriatric Cart and Menu of Items are a non-pharmacologic way to provide comfort*	Strongly agree; Somewhat agree; Neither agree nor disagree; Somewhat disagree; Strongly disagree
*The Geriatric Cart and Menu of Items are an important part of a comprehensive approach for improving patient satisfaction*	Strongly agree; Somewhat agree; Neither agree nor disagree; Somewhat disagree; Strongly disagree
*The Geriatric Cart and Menu of Items help increase my ability to care for older adults in a more compassionate way*	Strongly agree; Somewhat agree; Neither agree nor disagree; Somewhat disagree; Strongly disagree
*Having a hearing amplifier, reading glasses or magnifying glasses available for use helps patients feel more oriented/ less confused*	Strongly agree; Somewhat agree; Neither agree nor disagree; Somewhat disagree; Strongly disagree

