### Data management and statistical analysis

All study data will be collected and managed using Research Electronic Data Capture (REDCap) [30], a secure web-based application. Research assistants will use tablets with online access to the REDCap database for direct data entry and informed consent procedures.

For the primary objective evaluating the impact of the comfort menu and cart on the experience of older patients we will use the questionnaire adapted from Lichen et al. (2021) and McCusker et al. (2018). For the secondary objectives evaluating the impact of a comfort menu and cart on the experience of medical and multidisciplinary staff involved in caring for older patients treated in the ED, we will use the the questionnaire adapted from Lichen et al. (2021).

Data analysis will be performed using Stata version 17 (StataCorp, College Station, TX). All statistical tests will be two-tailed with an alpha error of 0.05. Numerical variables will be reported as means and standard deviations or medians and interquartile ranges (IQR) depending on their distribution, which will be assessed visually and using the D’Agostino-Pearson test for normality. Categorical variables will be described as absolute counts and proportions. Numerical variables will be compared using Student’s t-test or ANOVA for normal distributions and Wilcoxon or Kruskal-Wallis tests for non-normal distributions. As appropriate, categorical variables will be compared using the chi-square test or Fisher’s exact test. Analyses will be adjusted to account for potential confounding variables, such as baseline frailty, cognitive impairment, and clinical severity. Missing data will be handled though mixed effects model.

All relevant data from this study will be made available upon study completion.

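### Staff interviews run alongside patient recruitment in one ED, so clinicians very likely answer more than once, but the named tests assume independent responses

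*Protocol article*

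**What the plan says.** Staff experience is the first secondary objective. Under the staff interview heading, the article says "A trained research assistant will interview medical and multidisciplinary staff concurrently with patient recruitment". The Recruitment section places this in the ED of one hospital, with one assistant working 25 hours a week, for three months before and three months after the cart is introduced.

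The staff questionnaire has four items asked in both phases and four asked only after implementation. The first common item is about one patient: "During the patient’s stay in the ED, what was his/her average level of comfort". Another common item is worded around the respondent's own patient. The remaining two ask about age-friendly care and about general access to non-drug resources.

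The section on data management and statistical analysis gives one list of tests for the whole study. Numerical variables get a "t-test or ANOVA for normal distributions and Wilcoxon or Kruskal-Wallis tests for non-normal distributions", and categorical variables get chi-square or Fisher's exact tests. "All statistical tests will be two-tailed with an alpha error of 0.05". The examples of adjustment variables (frailty, cognition, severity) are all patient characteristics. The mixed model appears once, as the way to handle missing data, with no random effect specified. The article gives no number of staff, no number of interviews per clinician and no rule on repeat interviews.

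**The concern.** A two-sample comparison of staff answers is valid only if each clinician contributes one answer in the whole study. The described fieldwork makes that unlikely. If one interview accompanies each recruited patient, independence would need 2 × 132 = 264 different clinicians from one department, met during one assistant's shifts.

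Two departures from independence are possible, and they pull in opposite directions. Several answers from one clinician within a phase carry less information than the same number from different people, so the naive standard error is too small. Answers from one clinician in both phases form before-after pairs. Ignoring the pairing makes the naive standard error too large and wastes power. At stake are the confidence intervals and p-values for the staff-experience objective. The patient outcomes are not affected by this point.

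**Working it through.** **The plan's own figure.** The only sample size is for patients: "132 patients will be required in each group (pre- and post-intervention), totaling 264 participants". No staff figure exists to reproduce. The patient figure cannot be derived from the stated inputs either, because no standard deviation is given, but that has no bearing on the staff question. Below, 132 is borrowed as the number of staff responses per phase. This is an assumption.

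**Assumed inputs.** n = 132 responses per phase; K = 12, 22, 44 or 66 clinicians per phase, each giving m = 132/K = 11, 6, 3 or 2 responses; ICC (the share of variance due to the clinician) = 0.05, 0.10 or 0.30; f = the fraction of clinicians who answer in both phases, with a constant personal level.

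**Formula.** With total variance 1, the naive variance of the phase difference is 2/n. In the true variance, the effects of clinicians present in both phases cancel, which leaves 2(1 − ICC)/n + 2·m·ICC·(1 − f)/n. The ratio of true to naive variance is

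R = (1 − ICC) + m·ICC·(1 − f).

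- No overlap (f = 0): R = 1 + (m − 1)·ICC, the usual design effect.
- Full overlap (f = 1): R = 1 − ICC.
- R = 1 when m(1 − f) = 1. The naive error is too small when m(1 − f) exceeds 1 and too large when it is below 1.
- With one interview per clinician per phase (m = 1), R = 1 − f·ICC, so the test is still off unless no one answers in both phases.

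The actual type I error of a nominal two-sided 5% test is approximately 2·[1 − Φ(1.96/√R)].

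**Numbers put in.**
- K = 12, ICC 0.30, no overlap: R = 1 + 10 × 0.30 = 4.0; 1.96/2 = 0.98; error about 33%. Effective n = 132/4 = 33.
- K = 22, ICC 0.10, no overlap: R = 1 + 5 × 0.10 = 1.5; 1.96/1.225 = 1.60; error about 11%. Effective n = 132/1.5 = 88.
- K = 66, ICC 0.10, no overlap: R = 1.10; error about 6%.
- Any K, ICC 0.30, full overlap: R = 0.70; 1.96/0.837 = 2.34; error about 2%.

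**Simulation.** An unadjusted two-sample t-test under no phase effect, 4,000 runs per cell, agrees with the formula to about one percentage point. Entries are type I error at ICC 0.05 / 0.10 / 0.30.

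| Clinicians per phase (responses each) | No overlap | Half overlap | Full overlap |
|---|---|---|---|
| 12 (11) | 11 / 17 / 33% | 8 / 9 / 20% | 4 / 4 / 2% |
| 22 (6) | 8 / 10 / 21% | 6 / 7 / 12% | 4 / 4 / 2% |
| 44 (3) | 6 / 7 / 13% | 5 / 5 / 7% | 5 / 4 / 2% |
| 66 (2) | 5 / 6 / 8% | 5 / 5 / 5% | 4 / 4 / 2% |

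If the same 22 clinicians answer in both phases, but half of their personal variance is specific to the phase, the error is about 6 / 8 / 12%.

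**The case against.** The strongest reply is that repetition is not in the text. The article says when staff are interviewed, but not how many, how often, or whether once per patient. A clinician interviewed a single time about a single patient could answer every item. The interview is also said to follow the standard of the original comfort cart study, which may settle staff sampling and is not at hand. The department is large (over 80,000 visits a year, 22 private rooms) and the interviews cover several professions, so a wide pool of respondents is possible. The test list is generic, it assigns no test to the staff outcome, and details of secondary models are often left to an analysis plan.

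Much of this stands. Repetition and one interview per patient are inferences, and the size of the error cannot be computed from the article. Two things do not fall. First, the article is not silent on method: it names tests, and none of them, nor the adjustment or the mixed model as described, allows for a clinician who answers twice. Second, a later analysis plan cannot restore a respondent identifier that was not collected.

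A reader might also infer that staff results are bound to look too favourable, with false-positive rates well above 10%. The documents do not support this. The direction depends on how far the same staff answer in both phases. The highest rates need few clinicians, a high ICC and different people in each phase.

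**Conclusion.** The point holds in conditional form. If any clinician answers more than once, which is very likely in this setting but not stated, the named tests do not match the data for the four common staff items. Under the assumptions above, the type I error lies anywhere from about 2% to about 33%. It is close to nominal when few staff repeat (66 clinicians giving two answers each: about 5 to 6% at ICC 0.05 to 0.10 with no overlap). The four items asked only after implementation have no before-after test and are outside this point.

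One should not go further and say that the protocol has the same staff rating every patient, or that its staff p-values are certainly wrong. This concerns a secondary objective. It should be settled before recruitment, and it does not threaten the primary comparison.

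**What to change.** - State the sampling unit for staff interviews: whether one accompanies each patient, and whether a clinician may be interviewed again.
- Record a pseudonymous staff code with each interview, plus the patient's study number.
- Analyse the four common items with phase as fixed effect and a random intercept for staff, in an ordinal form suited to five or six response categories. Staff-clustered standard errors are an alternative, with caution if clinicians are few. Add a patient effect if several staff rate one patient.
- Optional: ask the general attitude items only once per clinician per phase, keeping the staff effect so that the pairing is used.

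The cost is one form field and a different model command. If few staff repeat, little is lost by the change. The drawback is that staff answers become linkable under a code, so the key needs protection and staff should be told. Timing matters: the schedule has the database being built until March 2026 and recruitment starting in April 2026, and the code cannot be recovered afterwards.

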**Table pone.0332773.t003:** 

Questions adapted from Lichen et al. (2021)	
* Question *	* Response options *
*During the patient’s stay in the ED, what was his/her average level of comfort?*	Very comfortable; Comfortable; Somewhat comfortable; Somewhat uncomfortable; Uncomfortable; Very uncomfortable
*I feel that age-friendly care specific to the geriatric patient’s needs was provided*	Strongly agree; Somewhat agree; Neither agree nor disagree; Somewhat disagree; Strongly disagree
*I currently have access to non-pharmacological resources to provide comfort for geriatric patients*	Strongly agree; Somewhat agree; Neither agree nor disagree; Somewhat disagree; Strongly disagree
*Offering non-pharmacological resources to my patient increases my work burden by too much*	Strongly agree; Somewhat agree; Neither agree nor disagree; Somewhat disagree; Strongly disagree
Additional questions in the post-implementation phase	
*The Geriatric Cart and Menu of Items are a non-pharmacologic way to provide comfort*	Strongly agree; Somewhat agree; Neither agree nor disagree; Somewhat disagree; Strongly disagree
*The Geriatric Cart and Menu of Items are an important part of a comprehensive approach for improving patient satisfaction*	Strongly agree; Somewhat agree; Neither agree nor disagree; Somewhat disagree; Strongly disagree
*The Geriatric Cart and Menu of Items help increase my ability to care for older adults in a more compassionate way*	Strongly agree; Somewhat agree; Neither agree nor disagree; Somewhat disagree; Strongly disagree
*Having a hearing amplifier, reading glasses or magnifying glasses available for use helps patients feel more oriented/ less confused*	Strongly agree; Somewhat agree; Neither agree nor disagree; Somewhat disagree; Strongly disagree

#### Follow-up interview.

A second research assistant, blinded to the initial assessment and ED care details, will conduct a phone interview 30 days (± 2 days) post-initial assessment. This interview will assess the following:

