### Data collection

#### Recruitment.

A trained research assistant will recruit participants in the ED, working 25 hours per week (five 5-hour shifts between 10:00 am and 10:00 pm) over six months (three months pre-intervention, from April 2026 to June 2026, and three months post-intervention, from July 2026 to September 2026). The assistant will conduct active searches for potential participants. Eligible patients will be invited to provide informed consent.

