**Table pone.0332773.t004:** 

ED readmissions	Number of ED visits since the initial visit
**Falls**	Number of falls since the initial visit
**Delirium incidence**	Assessed using the Family Confusion Assessment Method (FAM-CAM) [29] administered to a family member or caregiver
**Mood**	Assessed using the GDS-15
**Quality of life**	Assessed using the EQ-5D
**Functionality**	Assessed using the Katz Index, Barthel Index, and Lawton Scale
**Cognitive performance**	Assessed using the 10-CS
**Mortality**	If the patient has passed away, the date and cause of death will be recorded

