### Intervention

The comfort menu and cart will be implemented after the pre-intervention data collection phase is completed. The menu will list the items available on the cart and will be presented to eligible patients in printed or digital format (on a tablet). The cart will be placed in an easily accessible area within the ED. Approximated retail prices have been previously reported [3].

A one-month dedicated rollout period will precede the commencement of post-intervention participant enrollment. This phase is designed for comprehensive staff training on the proper use and components of the comfort menu and cart, including familiarization with all available items and menu options. Additionally, this period will ensure all necessary equipment is adequately prepared and any potential logistical challenges associated with the cart’s implementation are identified and resolved, thereby optimizing the fidelity and effectiveness of the intervention before data collection for the post-intervention group begins.

Comfort Cart Contents:

Hot and cold packs;Extra blanket and pillow;Face towel;Gloves and hat;Personal hygiene kit (toothbrush, toothpaste, cotton swabs, sleep mask, comb, deodorant, hand lotion);Items for distraction (magazines, word search puzzles, playing cards, coloring pages);Items to enhance communication (reading glasses, magnifying glass, penlight, cell phone charger, notepad, sound amplification device).

Comfort Menu Options:

Physiotherapy assessment;Conversation with chaplain, concierge, or social worker;List of resources for older adults needing community services;Home care assistance.

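### Blinding of the 30-day telephone assessor is partial: it does not reliably mask study phase, because the call date fixes the phase for at least about 95% of participants

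*Protocol article*

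**What the plan says.** Under Follow-up interview, the protocol article states: "A second research assistant, blinded to the initial assessment and ED care details, will conduct a phone interview 30 days (± 2 days) post-initial assessment". The table that follows lists what the call collects: ED visits and falls counted from the index visit, GDS-15, EQ-5D, Katz, Barthel, Lawton, 10-CS, mortality, and delirium, the last "Assessed using the Family Confusion Assessment Method (FAM-CAM) [29] administered to a family member or caregiver".

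Under Recruitment, the two groups are enrolled one after the other: "three months pre-intervention, from April 2026 to June 2026, and three months post-intervention, from July 2026 to September 2026". Under Intervention, "The comfort menu and cart will be implemented after the pre-intervention data collection phase is completed", and "A one-month dedicated rollout period will precede the commencement of post-intervention participant enrollment". The timetable under Expected results puts that rollout month in June 2026, alongside the last month of pre-intervention recruitment.

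The Secondary objectives call the 30-day outcomes exploratory. The section on ethics withholds details of the intervention from the consent form to limit information bias. No equivalent measure is described for the telephone assistant. The limitations in the Discussion mention self-report bias and the weaker causal basis of a before-and-after design, but not what the assessor may know about phase.

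**The concern.** In a sequential before-and-after study, exposure is a function of calendar time. A caller working at a fixed interval after enrolment can read the phase from the calendar, and withholding the baseline form does not change that. Respondents from the second phase may also mention the cart, and nothing in the article tells the caller how to prevent this.

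Most of the 30-day outcomes are scales administered by an interviewer or counts recalled on prompting. The Abstract and Expected results both anticipate a benefit. A caller who knows the phase and shares that expectation could, without intending to, prompt or score differently in the second phase. If the report then carried the word blinded over from the protocol, readers would probably take it to mean blinded to exposure. The 30-day outcomes also carry part of the study's claim to novelty in the Introduction and Discussion, so the description of how they were assessed should be accurate.

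**Working it through.** The plan gives no figure for how far dates reveal phase, so there is none to reproduce. The check enumerates call dates.

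**Inputs**
- Pre-intervention recruitment (Recruitment): "three months pre-intervention, from April 2026 to June 2026", taken as 1 April to 30 June, 91 days.
- Post-intervention recruitment (Recruitment): "three months post-intervention, from July 2026 to September 2026", taken as 1 July to 30 September, 92 days.
- Call window (Follow-up interview): enrolment date plus 28 to 32 days.
- Group size (Sample size calculation): 132 per phase, 264 in total.
- Assumptions: recruitment runs from the first to the last day of the named months, and accrual is even within each phase.

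**Step 1. Range of call dates**
- Pre-phase: 1 April + 28 = 29 April, to 30 June + 32 = 1 August.
- Post-phase: 1 July + 28 = 29 July, to 30 September + 32 = 1 November.
- Dates compatible with both phases: 29 July to 1 August, four dates.

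**Step 2. Most participants who could be ambiguous**
- Pre-phase enrolments whose window reaches 29 July: 27 to 30 June, 4 of 91 days. 132 × 4/91 = 5.80.
- Post-phase enrolments whose window starts by 1 August: 1 to 4 July, 4 of 92 days. 132 × 4/92 = 5.74.
- If all of them were called on an overlap date: 5.80 + 5.74 = 11.54. Identified: (264 − 11.54)/264 = 252.46/264 = 95.6%.

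**Step 3. Expected number, calls spread evenly over the five window days**
- Pre-phase pairs of enrolment day and call day that land in the overlap: 1 + 2 + 3 + 4 = 10 of 91 × 5 = 455. 132 × 10/455 = 2.90.
- Post-phase pairs: 4 + 3 + 2 + 1 = 10 of 92 × 5 = 460. 132 × 10/460 = 2.87.
- Ambiguous: 2.90 + 2.87 = 5.77. Identified: 1 − 5.77/264 = 97.8%.

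**Step 4. Sensitivity**
- All calls at exactly day 30: pre-phase calls end on 30 July and post-phase calls start on 31 July. There is no overlap, so 100%.
- No recruitment in June because of the rollout: pre-phase calls end on 31 May + 32 = 2 July and post-phase calls start on 29 July. Again 100%.
- Caller given the visit date to anchor the questions on falls and ED visits: 100% in every case.

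The 95.6% is the minimum over call timing, given even accrual. Heavier enrolment around the changeover would lower it; reaching 132 before 30 June would raise it.

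**The case against.** The strongest reply is that the article never claims masking to phase. It claims masking to the initial assessment and to ED care details, and much of that survives any call date. The caller need not know a participant's baseline GDS-15, EQ-5D, Katz, Barthel, Lawton or 10-CS scores, which avoids anchoring when the same scales are repeated. Nor need the caller know whether that participant used a cart item. A reader might infer from the calendar that the stated protection does not exist at all. The documents do not support that, and this part of the reply stands.

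Second, a date reveals phase only to someone who knows when the switch happened and that there was one. The article does not say the second assistant is told; it does not say this is withheld either. So the inference that the caller will in fact be unmasked is also not supported. What stands against the plan is narrower: the masking it describes does not by itself conceal phase.

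Third, how an assessor is kept blind is operational detail that an article may leave to the full protocol. That is fair for the procedures. It does not settle the point, because the article makes a statement about blinding to ED care, and its own calendar weakens that statement for cart availability.

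Fourth, the affected outcomes are exploratory. The primary experience questionnaire is taken at the initial interview, where no blinding is claimed. This is correct and limits the weight of the point. Finally, the check counts dates. It does not estimate a bias in any outcome, and nothing in the article allows one to be estimated.

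**Conclusion.** The point holds in limited form. The blinding is partial: it can cover individual baseline scores and individual cart use, but it does not reliably cover study phase. For a caller who knows the switch date, the call date fixes the phase for at least 95.6% of participants (about 252 of 264) and for about 98% with evenly spread calls. It does so for all of them if the caller has the visit date. These figures rest on calendar-month recruitment bounds and even accrual.

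The consequence is confined to the exploratory outcomes that depend on the interview: FAM-CAM, GDS-15, EQ-5D, Katz, Barthel, Lawton, 10-CS, falls and recalled ED visits. The primary experience outcome is untouched. The size of any resulting bias is unknown. The point still deserves correction because the remedy costs almost nothing and must be in place before the first calls, which on these dates could fall at the end of April 2026.

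**What to change.** The call date cannot be hidden, but its meaning can.

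1. Recruit and train the telephone assistant without describing the cart, the hypothesis or the go-live date. This extends to the assessor the concealment already planned for participants under Ethics and dissemination.
2. Use a fixed script that does not mention the cart, and ask respondents at the start not to describe their ED care.
3. Under Follow-up interview, state that masking covers individual baseline scores and individual ED care, and that masking to study phase is not assured. Step 1 may well work, so a flat statement that the caller is unmasked would go too far.
4. Add the same sentence to the limitations in the Discussion, and do not report the 30-day outcomes as blind-assessed for phase.
5. Check recalled revisits to the study hospital against the electronic record and the administrative databases already used for length of stay and costs (Chart review and administrative data). This covers visits to that hospital only and does nothing for the rated scales.

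The cost is protocol wording, a call script and one more field in a planned extraction. No additional patients or staff are needed. The downside is a slightly less favourable description of the 30-day outcomes.
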